## Abstract

**Background:**

Exercise training is an integral component of evidence-based management programs for many chronic cardiac and respiratory conditions. Despite this, there are limited high-quality studies available on the significance of exercise training in pulmonary hypertension (PH). The aim of this study is to evaluate the short and long-term effectiveness of exercise training in PH patients in terms of exercise capacity, quality of life, cardiac function and disease progression.

**Methods:**

This randomized control trial will aim to recruit 50 medically stable PH patients categorised as New York Heart Association functional classification II-III. Participants will be randomly allocated to either the supervised exercise training group or usual care group for the 8-week study period. Exercise training will be conducted in an outpatient setting. Measurements at baseline and following the 8-week study period include exercise capacity (6 min walk distance and cardiopulmonary exercise test), cardiac function (exercise cardiac magnetic resonance imaging [CMRI] and echocardiography), health-related quality of life (Cambridge Pulmonary Hypertension Outcome Review), adverse responses to exercise training and time to clinical worsening. In addition, participants will be followed up for a minimum of 2 year period from commencement of the study so as to monitor long-term clinical outcomes i.e. time to clinical worsening.

**Discussion:**

This study will determine whether an 8-week outpatient based supervised exercise training program is safe and beneficial for medically stable PH patients in the short and long term. This will be the first study to examine the impact of exercise training on right heart function using exercise CMRI. Results from the study will contribute new knowledge in relation to the impact of exercise training on cardiac function, long-term prognosis and inform clinical practice guidelines for this patient population. Moreover, the study will add to our understanding regarding the efficacy of exercise training in individuals with PH in an outpatient setting.

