### Intervention group

Participants randomly allocated to the intervention group will participate in an 8-week, twice weekly outpatient supervised exercise training program. The exercise training program will be conducted in an outpatient rehabilitation setting and supervised by an experienced physiotherapy clinician who will closely monitor the participants’ exercise performance and provide appropriate exercise progression. Details of exercise training sites can be obtained at the Clinical Trial Registry ACTRN12616001467426.

The aim is for each participant to complete 20 min each session of cycling and treadmill exercises (40 min in total). Each participant will commence training in the first session by undertaking a minimum of 10 min of cycling and 10 min of treadmill training. Interval training, consisting of 60 s of exercise and 120 s of rest, will be used if participants are unable to complete 10 min of continuous exercise. The duration of cycling and treadmill exercises will be up-titrated such that participants are completing 20 min each session of cycling and treadmill exercises by the end of the second week.

The initial treadmill speed will be set at 60–70% of six-minute walk test (6MWT) speed and titrated up to 90% of 6MWT speed as tolerated over the first 4 weeks of training, by monitoring training heart rate (HR), rating of perceived exertion (RPE) and leg fatigue on the modified Borg scale will be determined. Training intensity will be maintained at this HR and RPE for the remainder of the 8-week training period. An upper limit for exercise intensity will be set at 85% of age-predicted maximum HR and 4 on the 0–10 modified Borg RPE scale. Cycle intensity will be calculated using the 6MWT distance from standard equations [21]. The initial cycle training intensity will be prescribed at 60% of the estimated peak work rate from the 6MWT distance.

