Participants will be monitored during training so that their HR is less than 85% of peak 6MWT HR, oxygen saturation (SpO_2_) is above 85%, and RPE is between 3 to 4 on the modified Borg RPE scale. If required, supplemental oxygen will be provided during exercise sessions to maintain SpO_2_ above 85%. Each exercise training session should take approximately 45 to 60 min to complete. Exercise training will be discontinued for participants who suffer any adverse events (including syncope, dizziness or marked worsening in oxygen desaturation during exercise) during exercise training. These participants will be referred to their physician (JF) for assessment and evaluation for suitability to continue the study.

Following the exercise training program, participants will be prescribed a standard home exercise training program. The home exercise program will consist of the participant being asked to walk 3–5 times per week for 20–30 min. Participants will be asked to walk at an RPE similar to which they achieved during the exercise training program. Compliance with the home exercise program will be evaluated at subsequent clinic visits.

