### Control group

The control group participants will continue with their routine medical care and physical activity regimes for the 8-week study period without the additional exercise training intervention. During the 8-week period, participants allocated to the control group will receive a weekly phone call from the study coordinator to review any adverse events and to record exercise habits.

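### The long-term claim credits the 8-week supervised block alone, but the 2-year comparison is of supervised training plus prescribed home walking versus usual care

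*Protocol article*

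**What the plan says.** The protocol article describes the two arms and the long-term comparison in several places.

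- **Abstract, Discussion.** The question that the trial is said to settle is if the "8-week outpatient based supervised exercise training program is safe and beneficial for medically stable PH patients in the short and long term".
- **Abstract, Methods.** Participants are "randomly allocated to either the supervised exercise training group or usual care group for the 8-week study period". No home programme is mentioned there.
- **Intervention group.** The arm first receives an "8-week, twice weekly outpatient supervised exercise training program". Then: "Following the exercise training program, participants will be prescribed a standard home exercise training program". Participants are "asked to walk 3–5 times per week for 20–30 min", and "Compliance with the home exercise program will be evaluated at subsequent clinic visits". No end date is given for the home programme.
- **Control group.** Controls continue with "routine medical care and physical activity regimes for the 8-week study period without the additional exercise training intervention". Their exercise habits are recorded through weekly calls during those 8 weeks. The section gives no later condition or record.
- **Secondary outcome measures and Data analysis.** Survival and time to clinical worsening are followed for 2 years at clinic visits every 3 to 6 months. The index date is the start of the exercise programme or of the control period, and the analysis is by intention to treat.

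Elsewhere the wording varies. The abstract's aim and the objective in the Background speak of exercise training in general. The hypothesis in the Background and the specific aims in the main Discussion attach the long-term benefit to supervised training.

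**The concern.** The intervention named in the long-term conclusion is not the one that the 2-year follow-up compares. If the exercise arm does better at 2 years, the supervised block, the home walking or both could be responsible, and a reader of the abstract would credit the supervised block alone. That matters for practice: a service that adopted only the 8-week programme would be relying on a result obtained with continued home exercise prescribed afterwards.

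The article itself separates the two phases when it discusses earlier trials. The Background reports that gains in the inpatient period were larger than those in the home period that followed.

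The second half of the concern is the exercise record after week 8. It is described for one arm only. If the arms turn out similar, the data as described could not show whether controls had taken up exercise. The later trials for which this outcome is offered as pilot data would need that information.

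**Working it through.** The central check sets the stated claim beside the stated design.

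| | Named in the abstract's conclusion | Described in the methods |
|---|---|---|
| Exercise arm, weeks 1 to 8 | Supervised programme | Supervised programme, twice weekly |
| Exercise arm, after week 8 | Nothing | Prescribed home walking, 3 to 5 times a week, no stated end |
| Control arm, weeks 1 to 8 | – | Usual care and usual activity, no added training; weekly calls record exercise |
| Control arm, after week 8 | – | No condition or exercise record described |
| Exercise check after week 8 | – | Home-programme compliance, exercise arm |
| Time span of the claim | Short and long term | 2 years from the start of each arm's period |

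The two arms therefore differ by assignment in two components, and no arm receives the supervised block without the home programme. The randomised difference at 2 years estimates the joint effect. Nothing in the design separates the components.

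**How much of the 2 years the named component covers.** Taking 2 years as 2 × 52 = 104 weeks:

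- Supervised phase: 8/104 = 7.7% of the period. The remainder is 104 − 8 = 96 weeks.
- Supervised sessions: 8 × 2 = 16.
- Home sessions, assuming that the prescription runs unchanged to 2 years: 96 × 3 = 288 to 96 × 5 = 480.
- Supervised share of prescribed sessions: 16/(16 + 288) = 5.3% to 16/(16 + 480) = 3.2%.
- In minutes, with 40 min of exercise per supervised session: 16 × 40 = 640. Home walking is 96 × 3 × 20 = 5,760 to 96 × 5 × 30 = 14,400. The supervised share is 640/6,400 = 10.0% to 640/15,040 = 4.3%.

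Only the 8-of-104-weeks figure is free of the assumption about the home programme's length. None of these shares measures how much of an effect each component would cause.

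**Why a record in both arms matters.** The plan's own risk ratio reproduces: 0.26/0.64 = 0.41. Suppose a share c of controls took up exercise after week 8 and gained the full assumed benefit. This is my assumption and is not in the article. Control risk becomes 0.64(1 − c) + 0.26c.

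| c | Control risk | Risk ratio |
|---|---|---|
| 0 | 0.640 | 0.41 |
| 0.2 | 0.564 | 0.46 |
| 0.5 | 0.450 | 0.58 |

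Uptake by controls would dilute the contrast, and the record as described would not reveal it.

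**The case against.** The home programme is not hidden. It appears under the intervention group with its frequency, duration and intensity, so a careful reader sees a two-part intervention. Only one sentence, in the abstract, ties the 8 weeks to the long term; the stated aim and objective are broad enough to cover the whole strategy. The sample-size section already calls the clinical worsening outcome underpowered and offers it as pilot data. The document is also a condensed article, and the full protocol may say what controls are asked after week 8.

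Much of this stands, and it rules out several stronger readings.

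- **That the 2-year comparison is invalid.** A reader might infer this, but the arms are randomised, analysed by intention to treat and judged by a blinded panel. The comparison is sound for the strategy as a whole.
- **That control exercise goes unrecorded for 96 of 104 weeks.** The article describes a record only for the first 8 weeks. It does not say that none is kept later.
- **That controls will cross over.** Nothing in the text says so.
- **That the supervised block is a trivial part of the treatment.** The session shares rest on an assumed 96 weeks of home walking and do not measure effect.

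Two parts of the objection do not remove the point. Calling the outcome pilot data concerns precision, whereas the fault lies in which intervention is credited. And the mismatch between the abstract's conclusion and the intervention section is in this document, whatever a fuller one says.

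**Conclusion.** The point holds as a fault of attribution and description. The abstract assigns any long-term benefit to an 8-week supervised programme, while the 2-year contrast is that programme plus prescribed home walking against usual care. The contrast can support a claim about the strategy but not about the supervised block alone, which covers 7.7% of the period. Exercise after week 8 is described as checked in the exercise arm only.

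The 8-week outcomes, including the primary walking-test outcome, are unaffected, because home walking begins after the supervised programme ends. The conclusion rests on the text alone. It needs no assumption about how long the home programme lasts or how many controls take up exercise; those assumptions enter only the illustrations.

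**What to change.** 1. Restate the long-term objective and conclusion in the abstract's Discussion as the effect of 8 weeks of supervised training followed by a prescribed home programme, compared with usual care. Align the hypothesis in the Background and the specific aims in the main Discussion.
2. Keep the compliance check for the home programme. It is the only described measure of adherence to the second component.
3. At the routine visits every 3 to 6 months, add one identical question in both arms on exercise habits and any rehabilitation attended since the last visit. Keep the answers out of the material that goes to the blinded adjudicators, since they could reveal allocation.
4. Report uptake by arm beside the 2-year result.

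The cost is wording, plus one question per visit at visits already held. The drawback is a narrower claim: the long-term effect of the supervised block alone would no longer be asserted. No treatment or schedule changes.

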**Trial registration:**

Australia and New Zealand Clinical Trials Registry: ACTRN12616001467426. Registered 21st October, 2016.

## Background

Pulmonary hypertension (PH) is a complex condition that is defined as an elevation in mean pulmonary artery pressure of greater than 25 mmHg at rest [1] and pulmonary capillary wedge pressure less than 15 mmHg. It has multiple pathogenetic mechanisms and is typically a progressive disorder that can lead to right heart failure and premature death [2]. Whilst recent advances in medical therapy for PH have extended the time to clinical worsening, many patients continue to experience exertional symptoms of dyspnoea and fatigue which, in turn, result in a reduction in functional capacity and quality of life (QoL) [3].

Given the reduced functional capacity in PH, it would appear logical to extrapolate the results of exercise training studies in other chronic cardiac and respiratory conditions to the PH patient population. In other chronic conditions, exercise training has well established safety and efficacy in terms of improving symptoms, exercise capacity and QoL, and thus is recognised as a fundamental management strategy [4]. Despite this, exercise training has not routinely been encouraged for patients with PH due to the concern that it may contribute to disease progression and an increased risk of serious adverse events [5, 6].

Recent studies have challenged these assumptions regarding the risks of exercise training in PH and suggested exercise can be both beneficial and safe, even for patients with severe disease [7, 8]. Indeed, recently published systematic reviews demonstrated improved exercise capacity and quality of life following exercise training in PH [9–12]. Based on the results of these studies, updated international guidelines now tentatively recommend (strength of recommendation, IIb) supervised exercise training in PH [13]. However, it has been recognised amongst PH clinical experts and the guideline authors themselves that current evidence is limited and that additional high quality studies are required to establish the efficacy and long-term effects of exercise training in PH [5, 13]. Limitations include a paucity of high quality randomised controlled trials (RCTs) and the fact that many of the studies have used a highly supervised exercise training conducted in an inpatient setting [13, 14]. Moreover, the authors recognise that the mechanisms for improvement following exercise training remain unknown as are the effects on long term outcomes [13].

Currently, the evidence base of high quality studies examining exercise training remains narrow [15]. To date, the results of only 4 small RCT’s have been published [8, 16–18]. Of these, three have been published by the same group of authors [8, 17, 18] using a supervised, 3-weeks inpatient exercise program. Although the training adaptations were more favourable during the intensive inpatient training period compared with the subsequent home program, the results of this expensive and impractical exercise training paradigm are difficult to translate to the outpatient rehabilitation models that are widely adopted in Australia and around the world. As a result, to date only one small RCT (*n* = 20) has been published by Chan et al. [16] which examined the impact of exercise training in an outpatient based environment.

Whilst there is preliminary evidence that exercise training improves skeletal muscle oxidative capacity in PH [19], there have been no studies on the effect of exercise training on right ventricular function, overall cardiac function and long-term prognosis. Further robust studies are therefore necessary to assess the efficacy and safety of outpatient-based exercise training programs and to determine the impact of exercise training on cardiac function and prognostic outcomes. As such, the objectives of the present study are to examine the safety and impact of outpatient-based exercise training on cardiac function, and short- and long-term clinical outcomes in medically stable patients with PH. We hypothesise that supervised outpatient-based exercise training is safe for the PH patient population and will result in clinically significant benefits in terms of a reduction in disease severity and delayed time to clinical worsening, as well as improved exercise capacity, QoL and cardiac function.

## Methods

### Study design

This study will be a randomised controlled trial using concealed allocation and blinded outcome assessors and data analysts. Figure 1 illustrates the flow of the study from recruitment and screening for eligible participants to follow-up outcome assessments and data analysis.

**Fig. 1 Fig1:**
[figure not shown]
Study flow chart

### Participants

Participants will be recruited over a 3 year period from the cohort of PH patients under the care of the Queensland Centre for Pulmonary Transplantation and Vascular Disease Unit at The Prince Charles Hospital, Brisbane, Queensland. Strategies for improving participant recruitment will include regular meetings with the PH clinical team and liaising with the primary PH physician (JF) and the PH assessment physiotherapist. Inclusion criteria include: age over 18 years, a confirmed diagnosis of PH based on the results of a right heart catheterization procedure (mean pulmonary artery pressure > 25 mmHg and pulmonary capillary wedge pressure < 15 mmHg) and New York Heart Association functional classification II-III. Eligible participants also will be on stable PH medical therapies and have had no exacerbations in the previous 3 months.

Participants will be excluded if they have had a change in their PH medication regime in the last 3 months or have significant co-morbidities including left-sided heart failure. Other exclusion criteria include pregnancy, recent history of light-headedness during exercise or syncope episodes in the last month and significant musculoskeletal and neurological conditions likely to adversely impact exercise performance. Patients will also be excluded if they have any of the contraindications to exercise as per the American College of Sports Medicine (ACSM) guidelines [20].

Eligible participants will be contacted by a member of the research team and provided with verbal and written information regarding the study. Informed written consent will be obtained prior to participation in the study. The study has been approved by the Metro North Hospital and Health Service - The Prince Charles Hospital Human Research Ethics Committee (HREC). Changes to the protocol will be approved by the HREC. The trial is registered with the Australia and New Zealand Clinical Trials Registry: ACTRN12616001467426.

### Randomisation

Eligible participants will be randomised into parallel groups with a 1:1 allocation ratio to either the exercise training group or the control group after completion of the baseline measures. A concealed allocation procedure will be performed by a blinded investigator using permuted block randomisation of 10 subjects and sealed, opaque envelopes. This schedule will ensure a close balance in the number of participants assigned to each group.

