### Sample size and power calculations

A total of 50 participants will be recruited into this study. We have allowed for a 10% drop out over the 8-week period to ensure that 45 participants will complete the study. Where appropriate, sample sizes for the primary and secondary outcome measures have been determined using weighted effect sizes calculated from randomised controlled trials of exercise training in pulmonary hypertension [15].

For the primary outcome measure, i.e. change in the 6MWT distance, the study is powered at 0.91 using a 2-tailed test for independent samples and a weighted effect size of 1.01. For the peak exercise capacity ($$ \dot{\mathrm{V}}{\mathrm{O}}_{2\mathrm{peak}} $$), this study is powered at 0.95 using an pooled, weighted effect size of 1.10 [15]. The primary measure for QoL in the current study will be the CAMPHOR. For the role physical domain in the CAMPHOR, the study is powered at 0.90 based on a weighted effect size of 0.99 [15].

The principle measure for changes in cardiac function will be made using CMRI. Recently Addetia and colleagues suggested that a per group sample size of 23 participants would detect a 5% change in right ventricular ejection fraction [34] measured using CMRI with a power of 80% and the probability of a Type I error of 0.05. The authors suggest that for a 10% change in right ventricular ejection fraction, a smaller sample size of 6 participants would be required. Based on a conservative estimate of a 5% change in right ventricular ejection fraction, the current study would have approximately 80% power to detect changes in right ventricular systolic function.

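### A single published block size of 10 in an open, single-unit trial lets anyone with a full tally of allocations know on average 1 in 6 of them; varying, undisclosed sizes around 10 would cut this at little cost

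*Protocol article*

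**What the plan says.** All references are to the protocol article.

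- Randomisation: participants are "randomised into parallel groups with a 1:1 allocation ratio" once baseline measures are complete. The method is "permuted block randomisation of 10 subjects and sealed, opaque envelopes", and a blinded investigator carries out the concealed procedure. No other block size and no stratification factor is given.
- Study design: the trial uses "concealed allocation and blinded outcome assessors and data analysts". Participants, training staff and recruiters are not listed as blinded.
- Control group: control participants "will receive a weekly phone call from the study coordinator", so the coordinator knows who is in that arm.
- Intervention group: a physiotherapist supervises every training session in person.
- Participants: recruitment is from one pulmonary hypertension unit at one hospital over 3 years, supported by "regular meetings with the PH clinical team". Someone on the research team, not further specified, contacts eligible patients.
- Sample size and power calculations: "A total of 50 participants will be recruited into this study".

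**The concern.** Sealed opaque envelopes hide the next card, but they do not stop anyone from deducing it from the cards already opened. With a fixed 5 + 5 block whose size is public, an observer who counts allocations knows where each block ends. Once one arm has had its five, the observer knows every remaining allocation in that block. The last place in each block is always known.

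A recruiter with that knowledge could choose whom to approach, or when. Some eligibility criteria leave room for this because they call for judgement, such as whether co-morbidities are significant. The Background section records a concern that exercise may harm these patients, which could supply a motive. With about 25 participants per arm, a few steered entries could matter for the walk-distance comparison. Recruitment averages about 1.4 participants a month (50 / 36), slow enough for a count to be easy.

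**Working it through.** **Inputs.** Block of 10, 1:1 ratio (Randomisation); 50 participants (Sample size and power calculations). Assumed: no stratification, and all five blocks of 10 completed. The article gives no predictability figure to reproduce. As a check on its other figures, 22 + 23 completers and an effect size of 1.01 give power 0.912 by the noncentral t distribution, against the stated 0.91.

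**Certain allocations, fixed block of 10.** The number known in advance equals the length of the run of identical allocations that ends the block. A 5 + 5 block has C(10,5) = 252 sequences, and P(run of at least k) = 2 × C(10 − k, 5) / 252 for k from 2 to 5:

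- k = 1: 1
- k = 2: 2 × 56 / 252 = 0.444
- k = 3: 2 × 21 / 252 = 0.167
- k = 4: 2 × 6 / 252 = 0.048
- k = 5: 2 × 1 / 252 = 0.008

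The sum is 1.667 per block. This agrees with the closed form 2m/(m + 1) = 10/6 for a block of 2m. The share is 1.667/10 = 16.7%, or 5 × 1.667 = 8.3 of 50.

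**Best-guess rate, fixed block of 10.** The observer always guesses the arm with more places left and tosses a coin at ties. Full enumeration gives 65.3% correct, against 50% with no information.

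**Varying block sizes.** The comparison used 8,000 simulated trials of 50, with sizes drawn with equal probability. The observer knows the set of sizes and every past allocation but not the order of the sizes, and updates by Bayes' rule. This is the unfavourable case in which the set has leaked.

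| Block sizes | Certain | Best guess correct | Arms unequal at 50 |
|---|---|---|---|
| 10, fixed | 16.7% | 65.3% | 0% |
| 4, 6, 8 | 2.3% | 67.7% | 28% |
| 6, 8, 10 | 1.7% | 66.0% | 34% |
| 8, 10, 12 | 1.5% | 64.6% | 38% |

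With 8, 10 and 12, certain allocations drop from about 8.3 to about 0.7 of 50 (0.015 × 50). Correct guesses hardly move: (0.653 − 0.646) × 50 is about 0.35.

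**Cost in balance and power.** With 8, 10 and 12, the 95th percentile of the difference between arms is 2 and the largest seen was 6. For an effect size of 1.01, power is 0.938 at 25:25, 0.938 at 24:26 and 0.935 at 22:28.

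**The case against.** The strongest reply is that the 1 in 6 describes an observer the article never identifies. That person would need a complete, ordered record of allocations and also some influence over who is approached. The article assigns allocation to a blinded investigator. It does not say that the coordinator recruits, and it refers to training sites in the plural, so one physiotherapist need not see every trainee. Randomisation follows the baseline tests, so a recruiter would have to act at first approach and then predict that patient's place in the queue. This stands: the figure is conditional, and no size of bias in walk distance can be derived from it.

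A second reply is that 10 is already a sensible choice. Fixed blocks of 4, 6 and 8 leave 33%, 25% and 20% of allocations certain. That is true, but varying sizes around 10 do much better on certainty with no higher guess rate.

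A third is that the Data analysis section plans a stratified log-rank test without naming strata, so randomisation might be stratified. The Randomisation section names no strata, but this remains an assumption, and the count of five blocks rests on it.

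Finally, a condensed article may leave custody of the list to the full protocol. That is accepted, and its absence is not part of this point. The block size, by contrast, is stated.

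**Conclusion.** The point holds as a conditional weakness in a stated design choice. Anyone who knows the block size and holds a full tally can know 16.7% of allocations, about 8 of 50, assuming unstratified randomisation and complete blocks. The coordinator's calls and the supervised sessions make such a tally plausible, but the article does not show that recruiters have one.

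A reader might infer that one in six allocations will in fact be foreseen, or that concealment has failed. The article does not support either reading. A reader might also infer that random block sizes would remove the problem at no cost. They would not: the best-guess rate stays near 65%, about 1.5% of allocations remain certain if the set of sizes is known, and exact balance is no longer guaranteed. What the change does is cut certain predictions roughly elevenfold (16.7 / 1.5) even with the set known, for a very small price.

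**What to change.** For allocations not yet made, generate a new list with block sizes varying at random around 10, for example 8, 10 and 12. Do not use a small set such as 4, 6 and 8. Do not disclose the sizes to recruiting staff, or in any public document, until recruitment closes. The published size of 10 cannot be withdrawn, but it would no longer describe the remaining sequence.

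State in the protocol whether randomisation is stratified and whether those who approach patients are kept unaware of past allocations. If they are, the exposure is smaller and the protocol should say so.

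The cost is one new list, a short amendment and the possible small inequality of arms described above. The sample size need not change.
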